### Key secondary endpoint(s)

Relapse rate at late follow-up (LFU-1) 6 months after the start of treatment, and time to relapse; exacerbation rate at late follow-up (LFU-2, one year after start of treatment), and time to next exacerbation; clinical cure rate at the EOT visit and clinical cure rate at the TOC visit (both determined by patient-reported outcome (diary cards). Spirometry will be assessed at LFU-2 to assess long-term consequences.

Assessment of safety:

### Key criteria for safety are

Adverse eventsSerious adverse eventsIncidence of complications (Need for intensive care unit treatment, need for ventilatory support)Vital status

### Statistical analysis

#### Efficacy/test accuracy

A patient is classified as a treatment failure if additional antibiotic therapy is required during treatment period or until the test of cure visit (TOC at day 30, primary endpoint).

The primary analysis will be stratified for centre. A two-sided 95%-confidence interval will be computed for the difference in failure rates for placebo minus experimental treatment group. The null-hypothesis of relevant inferiority of the placebo treatment will be rejected in favor of the alternative that antibiotic treatment is not required in this patient population, if the upper bound of the confidence interval does not exceed 10%, which is standard for the comparison of antibiotic treatments. The primary analysis will be conducted on the ITT-population including all randomized patients that have taken experimental drug or placebo at least once. A conservative rule will count missing values in the placebo-group with treatment failure, and as success in the active treatment group.

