
It is remarkable that on this brittle basis, antibiotic treatment for AE-COPD is recommended for patients with severe exacerbations or severe underlying COPD [8]. Moreover, most AE-COPD are mild to moderate and not severe and it seems difficult to extrapolate the findings from one positive ICU study to the less severe situations.

In conclusion there still is no clear recommendation for antibiotic treatment for these patients. These facts underline that a randomized, placebo-controlled trial on antibiotics for mild to moderate AE-COPD is warranted [8]. In light of the fact that respiratory viruses are detected in 50% of exacerbations a major task is the reduction of unnecessary antibiotic treatment in patients with mild to moderate COPD exacerbations to stop the threatening increase in AB resistance [8]. It has been convincingly shown that prudent reduction of antibiotic use results in a decrease of bacterial resistance without an increase in complications [14]. Taken this important aspect into account it seems that the risk-benefit ratio of antibiotic treatment for mild to moderate AE-COPD is negative and should therefore be discouraged. The most recent study [15] showed that it is safe to treat AE-COPD patients with all grades of disease severity (GOLD 1 to 4) with placebo if standardized treatment is provided. All studies performed so far were designed to prove efficacy of antibiotics in AE-COPD [8].

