### Key inclusion criteria

Patients will be enrolled into the study when diagnosed with moderate acute exacerbation of COPD according to the definition of the Global initiative for chronic Obstructive Lung Disease (GOLD) without respiratory failure or need for intermediate or intensive care if they fulfill the following criteria:Male and non-pregnant female adults, older than 40 years of age, diagnosed with COPD stages I-IV as defined by GOLDDoctor’s diagnosis of acute (onset < 7 days) moderate exacerbation of COPD (definition see 3.2), necessitating the administration of systemic corticosteroidsProcalcitonin level < 0.25 ng/mL (to rule out community acquired pneumonia or lower respiratory tract infection with a clear indication for antibiotic treatment)Smoking history of 10 Pack Years or more

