### Sample size calculation

A limited number of studies have compared antibiotic treatment to placebo in patients with AE-COPD. Jorgensen et al. [20] found in 1992 a 63% success rate with placebo as compared to 64% with Amoxicillin after 7 days of treatment of uncomplicated exacerbations of chronic bronchitis. In contrast Anthonisen et al. [21] found in 1987 a 55% success rate with placebo and a 68% response rate with antibiotic treatment for 10 days. Daniels et al. [15] observed in 2010 a clinical success in the first study using a standardized treatment including systemic corticosteroids in 61% of patients from the doxycycline group and 53% from the placebo group. In all these studies background standard of care has not been optimized and it is assumed that this is the reason for observed differences in small studies. It is thus assumed that the response rate in the study population will be in the order of 65%. With a one-sided type 1 error of 2.5% 479 patients per group have to be recruited to reject the null-hypothesis of relevant inferiority of placebo treatment with 90% power and a non-inferiority margin of 10%. (Sample-size calculation has been performed with nQuery-Advisor 7.0).

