The sample size of this trial is assumed to be sufficient to determine changes in relapse rates, time to relapse, clinical cure rates at EOT and TOC and to assess long-term consequences of sparing anti-biotic treatment.

This is a randomized and double-blind clinical trial with placebo matching tablets for active treatment. Block-randomization will be used. Randomization will be stratified for centre. All randomized patients that have received study medication at least once will be included into the primary intention-to-treat (ITT)-analysis. This is a non-inferiority trial and usually a per-protocol analysis would be used as primary analysis. However, the impact of potential missing values could be anti-conservative in the per-protocol analysis when demonstrating non-inferiority to placebo as well (pts with no improvement to placebo drop) and the ITT population is used here with a strategy that should maximize differences between treatment groups in case of uncertainty about outcome, because irrelevance of differences between treatment strategies is the objective to be demonstrated. In this complex situation missing values will be counted as failure in the placebo-group and as a success for patients in the antibiotics group. It is obvious that all attempts have to be undertaken to follow all patients to the end of the study.

In conclusion we believe that ABACOPD will be the first sufficiently powered double-blind placebo-controlled study in the field to systematically assess the question whether antibiotics, known to increase antibiotic resistance, are really needed in a well-defined patient cohort receiving state-of-the art treatment in all other aspects.

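### The centre-stratified primary analysis is valid, but adding GOLD stage as a main effect could narrow the decisive interval slightly if stage predicts failure

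*Protocol article*

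**What the plan says.** All places are in the protocol article.

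- **Efficacy/test accuracy:** "The primary analysis will be stratified for centre". No other factor is named. "A two-sided 95%-confidence interval will be computed for the difference in failure rates", taken as placebo minus antibiotic, and non-inferiority is concluded "if the upper bound of the confidence interval does not exceed 10"%.
- **Discussion:** "Randomization will be stratified for centre", in blocks. Centre is the only randomisation factor stated, so design and analysis agree.
- **Key inclusion criteria:** patients are "diagnosed with COPD stages I-IV as defined by" GOLD. The full severity range is admitted.
- **Background:** antibiotics are "recommended for patients with severe exacerbations or severe underlying COPD". This describes current recommendations.
- **Sample size calculation:** "With a one-sided type 1 error of 2.5% 479 patients per group have to be recruited", "with 90% power and a non-inferiority margin of 10"%, with an assumed response rate of about 65%. No gain from covariates is built in.

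**The concern.** The trial's conclusion rests on one number, the upper confidence limit for the risk difference. The population runs from GOLD I to GOLD IV, and centre-stratified blocks do not balance stage between the arms. The endpoint is the need for additional antibiotic therapy. It is plausible that this need rises with the severity of the underlying disease, since the Background ties antibiotic recommendations to that severity. If so, part of the variation in failure could be explained by a value already known at entry, and an analysis that uses centre alone treats it as noise. What is at stake is a little precision against the margin. Validity and type 1 error are not in question.

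**Working it through.** **1. Reproduce the plan's figure.** The inputs from Sample size calculation are failure 0.35 in both arms, margin 0.10, one-sided alpha 0.025 and power 90%.

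n = (1.960 + 1.282)² × 2 × 0.35 × 0.65 / 0.10² = 478.1, rounded up to **479 per group**, as stated.

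SE = √(2 × 0.35 × 0.65 / 479) = 0.03082. The 95% half-width is 1.96 × 0.03082 = 6.04 points. Power = Φ(0.10/0.03082 − 1.96) = 90.05%. The plan reaches its stated power without any covariate.

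**2. Gain from adjusting for GOLD stage.** Let R² be the share of outcome variance explained by stage, that is, the between-stage variance of the failure rate divided by p(1 − p). Adjustment multiplies the SE by √(1 − R²). The article gives neither the stage mix nor failure rates by stage, so both are assumptions here. The mix is set at 10/40/35/15% for stages I to IV, with no true treatment difference and 479 per group.

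Worked example, failure 25/30/38/48%:
- p = 0.35.
- Between-stage variance = 0.10 × 0.10² + 0.40 × 0.05² + 0.35 × 0.03² + 0.15 × 0.13² = 0.00485.
- R² = 0.00485 / 0.2275 = 0.021.

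| Assumed failure by stage (%) | R² | Half-width, points | Power |
|---|---|---|---|
| 35/35/35/35 | 0 | 6.04 → 6.04 | 90.1% → 90.1% |
| 30/33/37/40 | 0.004 | 6.05 → 6.03 | 90.0% → 90.1% |
| 25/30/38/48 | 0.021 | 6.04 → 5.98 | 90.1% → 90.7% |
| 20/29/39/52 | 0.038 | 6.04 → 5.93 | 90.0% → 91.1% |
| 15/26/43/58 | 0.076 | 6.07 → 5.83 | 89.8% → 91.9% |
| 12/25/43/60 | 0.092 | 6.05 → 5.77 | 90.0% → 92.5% |

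Each row uses its own mean failure rate, from 0.350 to 0.3565. A narrowing of about 0.5 point would need R² near 0.15 (half-width 5.57).

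**3. Simulation of the main-effects version.** The set-up was 958 patients, 22 centres, blocks of four, and a linear model with robust variance. Mean SE with centre only, then with centre plus GOLD (1,500 runs per scenario):
- no association: 0.03082 → 0.03087 (0.2% larger)
- 25/30/38/48%: 0.03082 → 0.03054 (0.9% smaller)
- 20/29/39/52%: 0.03083 → 0.03029 (1.8% smaller)
- 12/25/43/60%: 0.03088 → 0.02949 (4.5% smaller), power 91.1% → 93.7%

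A separate 3,000-run simulation of the last two gradients gave SEs 1.7% and 4.4% smaller, with 95% coverage kept. Power went from 91.4% to 92.5% and from 90.7% to 92.8%.

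**4. Crossing GOLD with centre.** Twenty-two centres by four stages gives up to 88 cells. Mantel-Haenszel risk differences were simulated over 3,000 runs. Under no to moderate association (the moderate case being 25/30/39/48%), the half-width was 6.20 to 6.26 with crossing, against 6.03 to 6.05 for centre alone. Under 15/26/43/58% both were 6.06. About 14 of the 958 patients fell in cells containing one arm only. Crossing loses precision or gains none, so the form of the adjustment matters.

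**The case against.** The strongest case against raising this is that nothing in the plan is wrong. The analysis factor is the randomisation factor, the interval is valid, and 479 per group gives 90% power as stated. The article plans to allocate 980 patients, against the 2 × 479 = 958 required. All of this stands.

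Several stronger readings are tempting and should be resisted:

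- **That the interval is certainly wider than it needs to be.** This requires stage to predict additional antibiotic use by day 30, and no section says so. The Background sentence concerns who is recommended antibiotics, and the article itself regards the evidence behind that recommendation as weak. The Background also cites a study in which placebo treatment was safe across all GOLD grades. With no association there is no gain.
- **That stage is recorded for every patient.** The criterion admits all four stages, so stage should be known. The article does not state that it is recorded as an analysis variable.
- **That chance imbalance in stage biases the result.** Such imbalance is ordinary sampling variation, which a valid 95% interval already covers.
- **That further covariates are excluded.** The article names only centre, but it is a condensed account. The full protocol or the analysis plan may already specify more.

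It is also fair to object that adding GOLD is not free in every form: step 4 shows that crossing it with centre can cost precision. That does not touch the main-effects model, where the simulated loss under no association is about 0.2% of the SE.

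**Conclusion.** The point holds as a conditional, low-severity suggestion. The centre-stratified analysis is sound and adequately powered on its own assumptions. If GOLD stage is prognostic, adjusting for it as a main effect narrows the half-width by about 0.01 to 0.12 points under weak to moderate gradients (about 0.1 to 1 point of power). Under steep gradients it narrows by about 0.2 to 0.3 points, worth about 2 points of power or slightly more. If stage is not prognostic, almost nothing is lost. The case rests on that asymmetry. All stage mixes and gradients are assumptions, since the documents give none, and the power figures assume equal true failure rates.

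**What to change.** Before unblinding, and unless the full analysis plan already does so, extend the primary analysis in Efficacy/test accuracy as follows. The risk difference (placebo minus antibiotic) is a standardised estimate with robust variance from a model with centre and GOLD stage as main effects. State that the two are not crossed into centre-by-stage strata. Keep the 10-point margin and the decision rule on the same risk-difference scale, and report the centre-only estimate as a sensitivity check.

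The cost is one sentence in the plan and a little more analysis work, plus a negligible loss of precision if GOLD stage is not prognostic. No extra patients or visits are needed. No new data are needed either, provided stage is recorded at entry, which should be confirmed.

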### Study populations

We have calculated that 1300 patients have to be assessed for eligibility to have 980 patients to be allocated to trial. Ultimately 960 patients will be analysed. The total duration of the trial is calculated to be 36 months. Based on the feedback of the study centres of our research network we have calculated that 22 German centers need to be involved to guarantee adequate recruitment.

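### The stated 90% power assumes no missing day-30 outcomes, but the primary analysis counts every missing outcome against placebo, so power falls to about 74% at 2% missing and 37% at 5%

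*Protocol article*

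**What the plan says.** Under Statistical analysis (Efficacy/test accuracy), the primary set is all randomised patients who took study medication at least once. The test is by confidence interval: "A two-sided 95%-confidence interval will be computed for the difference in failure rates for placebo minus experimental treatment group". Non-inferiority is concluded "if the upper bound of the confidence interval does not exceed 10" per cent. Missing outcomes are handled as follows: "A conservative rule will count missing values in the placebo-group with treatment failure, and as success in the active treatment group". The Discussion repeats the rule: "missing values will be counted as failure in the placebo-group and as a success for patients in the antibiotics group". It explains that the aim is to make the groups differ as much as possible where an outcome is uncertain, because irrelevance of the difference is what has to be shown.

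The Sample size calculation assumes a response rate of about 65% and states: "With a one-sided type 1 error of 2.5% 479 patients per group have to be recruited to reject the null-hypothesis" of relevant inferiority, "with 90% power and a non-inferiority margin of 10" per cent. The Discussion repeats this calculation. Neither place mentions missing outcomes. Study populations gives 980 patients allocated and then: "Ultimately 960 patients will be analysed". No reason is given for the 20 who drop out of the count. The Abstract and the end of the Discussion describe the trial as sufficiently powered.

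**The concern.** A quoted power should belong to the analysis that will be run. Here the analysis has a rule that pushes the estimate towards the margin by a known amount for each missing outcome, and the sample size appears to ignore it. Adding some patients to cover drop-out does not repair this, because the rule moves the expected difference itself as well as affecting the precision.

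At stake is how a failed trial would be read. If placebo and antibiotic were truly identical and a few per cent of outcomes were missing, the trial could miss non-inferiority through imputation alone. That result might be taken to mean that antibiotics are needed, which is the opposite of what the trial sets out to show.

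**Working it through.** **Inputs from the article.** One-sided alpha 2.5% (two-sided 95% interval), power 90%, margin 0.10, response 65% (failure p = 0.35), 479 per group. **Assumed, because the article gives no figure:** a share m of dosed patients without a day-30 outcome, equal in both arms and unrelated to outcome. Stratification by centre is ignored.

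**Step 1: reproduce 479.** Unpooled normal formula, true difference zero:

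n = (1.960 + 1.2816)² × 2 × 0.35 × 0.65 / 0.10² = 10.507 × 0.455 / 0.01 ≈ 478.1, rounded up to 479.

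This matches. The calculation therefore contains no true difference and no missing outcomes.

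**Step 2: effect of the rule on the expected difference.**

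- Placebo failure: p(1 − m) + m
- Antibiotic failure: p(1 − m)
- Difference: m, whatever p is

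Each 1% of missing outcomes uses one of the ten margin points.

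**Step 3: power under the rule.** Power = Φ((0.10 − m)/SE − 1.96), with SE = √[(pP(1 − pP) + pA(1 − pA))/479].

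Example, m = 2%: pP = 0.363 and pA = 0.343. SE = √[(0.2312 + 0.2254)/479] = 0.0309. Then 0.08/0.0309 − 1.96 ≈ 0.63, so power is about 74%.

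| Missing per arm | Placebo failure | Antibiotic failure | Expected difference | Power, 479 per arm |
|---|---|---|---|---|
| 0% | 35.0% | 35.0% | 0 | 90% |
| 0.5% | 35.3% | 34.8% | 0.5 points | 87% |
| 1% | 35.7% | 34.7% | 1 point | 83% |
| 2% | 36.3% | 34.3% | 2 points | 74% |
| 3% | 37.0% | 34.0% | 3 points | 62% |
| 5% | 38.3% | 33.3% | 5 points | 37% |

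Simulation (400,000 trials per setting) gave 73.6% at 2% and 36.3% at 5%. Using all 980 patients (490 per arm) changes little: 74.6% at 2% and 37.3% at 5%.

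**Step 4: dependence on the failure rate.** With p = 0.20 and m = 2%: pP = 0.216, pA = 0.196, SE = 0.0261, and 0.08/0.0261 − 1.96 ≈ 1.10, so power is about 86%. With nothing missing, the same p gives SE = √(0.32/479) = 0.0258 and power of about 97%. The loss is therefore about 11 points, against 16 at p = 0.35.

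**Step 5: type I error.** With a true difference δ, the rule gives an expected difference of (1 − m)δ + m. At δ = 0.10 this is 0.10 + 0.90m, never below the margin. The rule cannot make a false claim of non-inferiority more likely.

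**Step 6: 980 to 960.** The primary set excludes only patients who never took study medication. Twenty never-dosed patients would give 960, or 480 per arm, which just covers 479. On that reading the step makes no provision for missing outcomes among dosed patients.

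**The case against.** The strongest defence is that nothing in the calculation is wrong: 479 follows from the stated inputs. The placebo-adverse rule is a deliberate conservative choice with a stated rationale, and it protects against the more serious error. The endpoint is simple (whether further antibiotic was required by day 30), and the Discussion commits to every effort at follow-up, so missingness may be low. The article is also a condensed account, and an expected missing rate may stand in the full protocol.

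Most of this stands. The rule is defensible and the 479 is not an arithmetic error. The 2% and 5% rates are assumptions, and nothing in the article points to missingness near 10%, where failure would be almost certain. What remains is that the article prints the rule, the sample size and the power together, and they agree only if almost no outcome is missing; 0.5% already brings power to 87%.

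Two stronger readings are tempting. A reader might infer that the step from 980 to 960 is an accounting error, or that it shows an expected 2% of missing outcomes (20/980 = 2.04%). Neither is supported. Dosed patients without an outcome stay in the primary set and so would not reduce 980 to 960, whereas never-dosed patients would. A reader might also infer that the asymmetric rule should be replaced as the primary analysis. That is a trade-off between protection and power, not a fault in the document.

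**Conclusion.** The 90% power does not belong to the primary analysis as written unless nearly every dosed patient has a day-30 outcome. Under the design assumption of 35% failure in both arms, and with equal missingness unrelated to outcome, identical arms would fail to show non-inferiority in about 26% of trials at 2% missing and 63% at 5%, against the planned 10%. The size depends on the missing rate, which the article does not give, and on the failure rate, which it states only approximately. The consequence is overstated power and a greater risk of an inconclusive trial; validity is not affected.

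**What to change.** 1. In the Sample size calculation and its repeat in the Discussion, state the assumed rate of missing day-30 outcomes. Restate the power under the primary worst-case rule over a range of rates, for example as in the table above.
2. Qualify the description of the trial as sufficiently powered in the Abstract and the Discussion accordingly.
3. In Study populations, say what the 20 patients between 980 and 960 represent.
4. Optionally, keep the primary rule and report beside it a pre-specified multiple-imputation or tipping-point analysis, so that a failure caused by imputation alone can be recognised.

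Counting missing as failure in both arms should not be substituted. It shrinks a true difference by the factor 1 − m. With true failure of 45% against 35% and 479 per arm, one-sided type I error would rise from 2.5% to about 2.9% at 2% missing, 3.6% at 5% and 5.0% at 10%.

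The cost is wording and a less favourable stated power; no extra patients are needed. Restoring 90% under the rule is a separate decision and would take about 592 per arm at 1% missing, 750 at 2% and 1,926 at 5%.

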### Sample size calculation

A limited number of studies have compared antibiotic treatment to placebo in patients with AE-COPD. Jorgensen et al. [20] found in 1992 a 63% success rate with placebo as compared to 64% with Amoxicillin after 7 days of treatment of uncomplicated exacerbations of chronic bronchitis. In contrast Anthonisen et al. [21] found in 1987 a 55% success rate with placebo and a 68% response rate with antibiotic treatment for 10 days. Daniels et al. [15] observed in 2010 a clinical success in the first study using a standardized treatment including systemic corticosteroids in 61% of patients from the doxycycline group and 53% from the placebo group. In all these studies background standard of care has not been optimized and it is assumed that this is the reason for observed differences in small studies. It is thus assumed that the response rate in the study population will be in the order of 65%. With a one-sided type 1 error of 2.5% 479 patients per group have to be recruited to reject the null-hypothesis of relevant inferiority of placebo treatment with 90% power and a non-inferiority margin of 10%. (Sample-size calculation has been performed with nQuery-Advisor 7.0).

